### Image processing

All CT scans will be processed by the RITeS team as follows:

1)In DICOM (Digital Imaging and Communications in Medicine) format2)On the cloud-based e-ASPECTS platform available at https://brainomix.com
3)Anonymised prior to web upload to remove patient identifiers, but retaining original trial identifiers, using modiCAS DICOM anonymizer (Erlangen, Germany).4)A person, trained in CT scan handling, will manually select the relevant scan for each patient using four criteria: I. First CT scan acquired after the patient reached hospital, if more than one available.II.Ideally native images (i.e. non-reformatted) acquired axially, but reformatted scans will be accepted if native imaging not available.III.The thinnest CT slices if more than one image set available.IV.Scans acquired using a soft-tissue kernel.At this stage, all scans meeting these criteria will be processed agnostic of patient or imaging characteristics. Scan selection for entry into the representative RITeS dataset will occur only once processing is complete, blind to imaging appearances and software results (see below).5)Scans will be batched into zip files of 10+ scans and uploaded to the Brainomix cloud-based platform.6)Affected side information will not be included at this processing stage but will be entered separately later for a proportion of cases.7)Any scan upload or processing failures will be recorded in a spreadsheet.8)Results will be exported from the Brainomix platform, using the standard export function and stored securely offline in .csv format.

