## Abstract

**Background:** Artificial intelligence-based software may automatically detect ischaemic stroke lesions and provide an Alberta Stroke Program Early CT score (ASPECTS) on CT, and identify arterial occlusion and provide a collateral score on CTA. Large-scale independent testing will inform clinical use, but is lacking. We aim to test e-ASPECTS and e-CTA (Brainomix, Oxford UK) using CT scans obtained from a range of clinical studies.

**Methods:** Using prospectively collected baseline CT and CTA scans from 10 national/international clinical stroke trials or registries (total >6600 patients), we will select a large clinically representative sample for testing e-ASPECTS and e-CTA compared to previously acquired independent expert human interpretation (reference standard). Our primary aims are to test agreement between software-derived and masked human expert ASPECTS, and the diagnostic accuracy of e-ASPECTS for identifying all causes of stroke symptoms using follow-up imaging and final clinical opinion as diagnostic ground truth. Our secondary aims are to test when and why e-ASPECTS is more or less accurate, or succeeds/fails to produce results, agreement between e-CTA and human expert CTA interpretation, and repeatability of e-ASPECTS/e-CTA results. All testing will be conducted on an intention-to-analyse basis. We will assess agreement between software and expert-human ratings and test the diagnostic accuracy of software.

**Conclusions:** RITeS will provide comprehensive, robust and representative testing of e-ASPECTS and e-CTA against the current gold-standard, expert-human interpretation.

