## Methods

### Study design

We will test the accuracy of e-ASPECTS and e-CTA software for the automated assessment of CT scans performed acutely for suspected stroke among representative patients. We will compare e-ASPECTS/e-CTA with expert human readers who form the current reference standard. We will use CT scans from acute stroke trials that include a range of commonly encountered scan appearances including early ischaemia, haemorrhage, typical pre-stroke features and mimics. All scans have been rated by panels of experts representing many different individuals across these non-commercial trials. We will in addition, perform new human-ratings for a subgroup of the previously collected scans to compare the time needed for human versus e-ASPECTS assessment of CT and to assess the clinical impact of e-ASPECTS software on acute stroke care, i.e. whether it influences diagnostic confidence or alters treatment decisions.

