### Patient population

A clinically representative sample (equivalent to the patient population for whom e-ASPECTS or e-CTA may routinely be used) of baseline NECT brain and CTA scans will be selected from the following 10 multicentre national and international randomised-controlled trials (RCTs) and observational studies of stroke: Alteplase versus tenecteplase for thrombolysis after ischaemic stroke (ATTEST)^9^; European multicentre, randomised, phase III clinical trial of therapeutic hypothermia plus best medical treatment versus best medical treatment alone for acute ischaemic stroke (EuroHyp-1)^10^; Third International Stroke Trial (IST-3)^11^; Lothian study of INtraCerebral Haemorrhage Pathology, Imaging and Neurological outcome (LINCHPIN)^12^; Pragmatic Ischaemic Thrombectomy Evaluation (PISTE)^13^; POst-Stroke Hyperglycaemia (POSH)^14^; Penumbra and Recanalisation Acute Computed Tomography in Ischaemic Stroke Evaluation (PRACTISE)^15^; REstart or STop Antithrombotics Randomised Trial (RESTART)^16^; Rapid Intervention with Glyceryl trinitrate in Hypertensive stroke Trial-2 (RIGHT-2)^17^; Safe Implementation of Treatments in Stroke (SITS) open study^18^. These trials collectively include over 6600 individual patients accessible to RITeS; see Table 1 for individual trial numbers and details of available imaging.

All of these trials individually obtained research ethics committee approval. Consent was acquired from or on behalf of all recruited patients.

Baseline CT scans in these trials were scored using very similar methods (often using identical pre-validated schema, i.e. five of the trials used IST-3 methodology for scan assessment^19^, all studies of ischaemic stroke included ASPECTS scoring), and similar patient demographic baseline and outcome data were collected. Scan ratings were obtained by expert readers, nominated by the trials, without knowledge of any clinical baseline or follow-up data, follow-up scans or treatment. Expert rating included assessment for: ASPECTS^2^; acute ischaemia in brain regions other than the MCA territory^1^,^20^; acute intracranial haemorrhage^21^; structural stroke mimics, pre-stroke brain changes (brain atrophy, leukoaraiosis, old stroke lesions)^3^ and image quality. Baseline CTA scans were scored for: arterial obstruction location and extent^22^; collateral extent^23^. 

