## Statistical analysis

### Analysis principles and general considerations

Primary and where appropriate, secondary outcome testing will be conducted on an ‘intention-to-analyse’ basis irrespective of whether scan processing was successful or not◦ Processing will be considered successful when an ASPECTS (0-10) or CTA result (occlusion/no-occlusion or scalar collateral score) is provided, or when arterial hyperattenuation or haemorrhage is detected.◦ We will record all software failures whether these occur at the scan upload, scan processing, or results output stage.We will use mean (standard deviation, SD) or median (inter-quartile range, IQR) to represent the distribution of parametric and non-parametric data, respectively. We will use n (%) for categorical data.Where possible, we will use diagnostic accuracy statistics as the principal method in RITeS for comparing software and expert human results. With expert human results as the reference standard, we will calculate true/false positive/negative cases (TP, FP, TN, FN, respectively) and derive sensitivity (TP/TP+FN), specificity (TN/TN+FP), positive predictive (TP/TP+FP), negative predictive (TN/TN+FN), and accuracy (TP+TN/TP+TN+FP+FN) percentages as standard. We will calculate 95% confidence intervals for each using the Wilson score method^37^. ◦ For all diagnostic accuracy testing we will include random-effects meta-analysis modelling of individual patient data (i.e. a one-step meta-analysis) to provide overall estimates of sensitivity and specificity, to assess variation within and between the 10 RITeS studies, and to account for clustering of individual study results^38^,^39^.◦ For each of the 10 RITeS studies, we will use the PROBAST method for assessing risk of bias in diagnostic modelling^40^. For all comparisons of software and expert human results, we will review side of affected brain data to ensure ASPECTS and CTA results are correctly matched for each cerebral hemisphere, i.e. matched results require same score and side. We will separately test whether knowledge of affected side impacts the accuracy of e-ASPECTS results, see secondary outcomes below.Bland-Altman plots^41^ will be used to visually compare software and expert human results, comparing mean score differences to assess the magnitude, direction and distribution of error and will use ± 1.96 SD to determine the range of agreement^42^. For software and expert human results to be considered equivalent, we will set maximum clinically acceptable limits of agreement for individual scores, specified in the relevant sections below.Krippendorff’s Alpha^43^ (K-alpha) will be used to assess reader (human-human and human-software, as necessary) agreement. K-alpha is generally more robust than kappa in this context since it can handle categorical and ordinal data, works where there is missing data, adjusts for small sample sizes, and includes multiple observers simultaneously^43^,^44^. K-alpha results are interpreted similarly to kappa with scores ranging from -1 (perfect disagreement) to +1 (perfect agreement). We will therefore also use the Landis and Koch method for interpreting K-alpha results (as commonly used for kappa): 0.00–0.20=slight agreement, 0.21–0.40=fair agreement, 0.41–0.60=moderate agreement, 0.61–0.80=substantial agreement and 0.81–1.00=almost perfect agreement^45^.Other specific statistical tests are listed in the following sections.For multivariable testing, we will check for multicollinearity between included variables by identifying variance inflation factors (VIF) >5. Where multicollinearity is detected, we will run separate (but otherwise equivalent) multivariable regression models for each of the internally correlated variables.We will not impute but will report missing data (proportions of data missing for each variable and observations not included in analyses).We will use SPSS, IBM Corporation (Armonk, USA) and/or R (https://www.r-project.org/) statistical software for all analyses. We will preferentially report 95% confidence intervals, but where appropriate, we will report p-values.

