
### Primary outcomes

For these evaluations of e-ASPECTS, we will use a representative RITeS sample of NECT.

In two analyses, we will compare e-ASPECTS results to those provided by expert human readers for the assessment of non-enhanced brain CT acquired at baseline among patients presenting acutely with symptoms of stroke.

**
*Representative sampling for e-ASPECTS testing of primary outcomes.*
** Where clinical or demographic features are different to the comparator SSNAP/STTC/HERMES datasets (i.e. RITeS values should be within the range provided by the other datasets), we will use stratified random sampling to remove select cases (which are over-representing these features) to reduce these differences while maintaining the maximum sample size from the data available to RITeS. For example, if RITeS has 42% female patients and a median NIHSS of 19, we would identify all male patients with a high NIHSS and randomly remove subsets of these until the sex ratio and NIHSS are within the desired ranges. We will not select cases on the basis of the radiological features in Table 3.

To assess the impact of factors beyond our control which might affect the representativeness of our sample, we will perform sensitivity analyses of our primary outcomes for the following randomly selected subgroups: 1. With balanced representation from all RITeS trials, i.e. we will exclude surplus cases for trials which are relatively over-represented (more than double the median trial contribution).2. Where non-stroke mimics represent 26% of the total sample.

**
*1. Difference in ASPECT scores of e-ASPECTS and expert human readers.*
** We will compare e-ASPECTS and expert human results using overlapping histograms and Mann-Whitney U testing to assess the distribution of results, and Wilcoxon signed rank testing and Bland-Altman plots to assess pairwise agreement for each case. For results to be considered equivalent on Bland-Altman testing, we expect the range of agreement to be within ± 2 ASPECTS points. This is an arbitrarily derived but clinically meaningful difference that might lead to alterations in treatment for individual patients based on the thresholds presented below. We will also use K-alpha statistics to assess software-human reader agreement for these scalar data.

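### The rule choosing the software's CT input is not tied to the scan or series behind the stored expert rating, and no scan or series match is recorded

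*SAP article*

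**What the plan says.** Under Image processing, a trained person "will manually select the relevant scan for each patient using four criteria". Criterion I is "First CT scan acquired after the patient reached hospital, if more than one available". Criterion II prefers native axial images. Criterion III is "The thinnest CT slices if more than one image set available". Criterion IV asks for a soft-tissue kernel. The rule therefore foresees both several scans and several image sets for one patient.

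The comparator was produced earlier. The Abstract describes expert readings that already exist, and Patient population says "Baseline CT scans in these trials were scored using very similar methods". Study design adds "All scans have been rated by panels of experts representing many different individuals across these non-commercial trials". None of these places says which series or slice thickness the experts viewed. New readings are planned only for the timing and clinical-impact work, not for the primary outcomes.

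The only stated check that software and expert results belong together is in Analysis principles and general considerations, where side data are reviewed "to ensure ASPECTS and CTA results are correctly matched for each cerebral hemisphere, i.e. matched results require same score and side".

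For primary outcome 1, the Bland-Altman criterion is "we expect the range of agreement to be within ± 2 ASPECTS points", with limits set at ±1.96 SD.

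**The concern.** A paired agreement analysis attributes the whole within-pair difference to the raters. That is sound only if both raters worked from the same images. Here one rule picks the software's image, while the expert's image was fixed years earlier by ten separate trials. Nothing in the plan connects the two below the level of the patient.

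Where they differ, the difference has three routes into the results:

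- It widens the Bland-Altman limits that are judged against ±2 points.
- With the expert score as reference, it can move a case across an ASPECTS cut-point and be counted as a false positive or false negative.
- It enters the absolute ASPECTS difference modelled under Secondary outcomes, item 1. Slice thickness (≤1 mm versus >1 mm, Table 5) is a predictor there and describes only the software's input. Where several image sets exist, the software always receives the thinnest. If the expert read a thicker one, the mismatch tends to fall in the thin-slice category. The coefficient then mixes software performance on thin slices with the expert having read something else.

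Primary outcome 2 is different. Software and baseline readers are both judged against expert opinion with follow-up data, so unequal input could favour either side.

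**Working it through.** **Is the gap closed elsewhere?**

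| Level | What the plan says | Closed? |
|---|---|---|
| Patient | Trial identifiers are kept at anonymisation | Yes |
| Side | Side data are reviewed for every comparison | Yes |
| Scan | Pool is baseline scans described as rated; first hospital CT if several | Largely, but by description and not by a rule |
| Series | Thinnest set to the software; expert's set not stated | No |

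**What the ±2 criterion allows.** The limits are ±1.96 SD, so the largest SD of differences that meets ±2 is 2/1.96 = 1.02 (variance 4/3.8416 = 1.0412). The plan gives no expected SD and no mismatch rate. Everything below rests on assumed values and shows a range.

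**Undirected mismatch (the series case).** Let SD0 be the SD of differences on identical images. Let a share f of cases carry an extra independent difference with mean 0 and SD e, and let the overall mean difference be 0. Then

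limits = ±1.96 × √(SD0² + f·e²).

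| SD0 | f | e | Variance | Limits | Within ±2? |
|---|---|---|---|---|---|
| 0.8 | 10% | 1.5 | 0.64 + 0.225 = 0.865 | ±1.82 | yes |
| 0.8 | 20% | 1.5 | 0.64 + 0.45 = 1.09 | ±2.05 | no |
| 0.9 | 10% | 1.0 | 0.81 + 0.10 = 0.91 | ±1.87 | yes |
| 0.9 | 20% | 1.5 | 0.81 + 0.45 = 1.26 | ±2.20 | no |
| 0.9 | 30% | 1.0 | 0.81 + 0.30 = 1.11 | ±2.06 | no |
| 1.0 | 5% | 1.0 | 1.00 + 0.05 = 1.05 | ±2.01 | no |

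Solving for the share that just reaches ±2 gives f = (1.0412 − SD0²)/e²:

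| SD0 | e = 1 | e = 1.5 | e = 2 |
|---|---|---|---|
| 0.8 | 40.1% | 17.8% | 10.0% |
| 0.9 | 23.1% | 10.3% | 5.8% |
| 1.0 | 4.1% | 1.8% | 1.0% |

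**Directed mismatch (only if a different scan was used).** With a constant shift d in a share p, the variance is SD0² + p·d² − (p·d)² and the mean moves by p·d. Take d = 2 and no bias on identical scans.

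- SD0 = 1.0, p = 5%: variance 1 + 0.20 − 0.01 = 1.19, half-width 2.14, mean 0.10, outer limit 2.24.
- SD0 = 1.0, p = 20%: variance 1 + 0.80 − 0.16 = 1.64, half-width 2.51, mean 0.40, outer limit 2.91.
- SD0 = 0.8, p = 5%: variance 0.64 + 0.19 = 0.83, half-width 1.79, mean 0.10, outer limit 1.89.

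The outcome depends heavily on SD0. At 1.0 the limits are already ±1.96 before any mismatch.

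The sample-size figures (494, 500 and 725) are not affected by this point.

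**The case against.** The strongest reply is that the scan-level question is largely handled. The material is the trials' baseline CTs, described as rated. Table 1 lists follow-up CT or CT/MRI for all eight ischaemic studies, so a first-CT rule reads naturally as a device to keep follow-up scans out. This stands: scan mismatch can arise only in patients with more than one eligible hospital CT, and is probably uncommon.

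A reader might infer that the software is given an earlier scan than the experts read, for example after transfer for thrombectomy, so that its ASPECTS is systematically too high. The document does not support that. It nowhere describes a rescan before trial entry or a rating of a later scan. The two thrombectomy studies contribute 65 + 293 = 358 of 5,128 patients in the ischaemic studies (7.0%). That route alone could not produce a 20% mismatch, which needs about 1,026. For the series gap the direction argument fails altogether, because two reconstructions of one acquisition show the brain at the same moment.

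It is also fair to say that slice thickness of the software's own input is a proper covariate for the software's accuracy. But the dependent variable is the distance from the expert, and that distance may also depend on which series the expert read. Table 5 has no variable for this.

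Could the linkage be left to a fuller plan? The article writes the selection rule out criterion by criterion, so the missing link is part of what it fixes.

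**Conclusion.** The point holds in a limited form. The plan fixes how the software's image is chosen without linking it to the rated image, and it checks only side. At scan level the exposure is probably small. At series level the gap is open, with unknown frequency and unknown direction.

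The document does not show that the ±2 criterion will be missed for this reason. Under the assumed values, some settings pass and others fail. What it does show is little slack: the criterion tolerates an SD of at most 1.02, so a moderate mismatch could decide the result if like-for-like agreement is near that bound. Nor can all input differences be called software error. That description fits the analyses with the stored expert reading as reference, chiefly primary outcome 1 and the accuracy regression. It does not fit primary outcome 2.

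A change is worth making because it is cheap and would turn an unknown into a reported number.

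**What to change.** 1. Amend criterion I: where more than one hospital CT exists, process the acquisition that the trial's panel rated, identified by scan date and time. Use the first hospital CT only if the rated scan cannot be identified.
2. Keep the thinnest-series rule, but record for each case whether the scan and, where known, the series match the expert reading.
3. Report the numbers matched, unmatched and unknown at each level.
4. Keep all cases in the primary analysis. Restricting it to verified pairs could discard correctly matched cases only because records are missing, against the plan's aim of the largest possible sample.
5. Add a sensitivity analysis, restricted to confirmed same-scan cases, of primary outcome 1 and of the accuracy regression containing slice thickness.

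The cost is a date and time check against the trials' reading records, with a smaller sample in the sensitivity analysis only. The check need not reveal imaging appearances or results, so it is compatible with the blinding described under Image processing. No new readings are needed.

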### Secondary outcomes

**
*1. e-ASPECTS processing success and factors influencing accuracy.*
** To present the most complete picture available, we will use the entire RITeS sample for these analyses (i.e. not just the representative sample) but we will also include a sensitivity analysis of the representative sample.

We will report the proportion of scans successfully and unsuccessfully processed by e-ASPECTS and collate reasons cited by e-ASPECTS for any processing failures. We will use summary statistics to describe and compare the subgroups of scans that were successfully versus unsuccessfully processed. This will include patient and radiological factors (see Table 4).

To determine the influence of patient and radiological factors on the accuracy of ASPECTS results produced by e-ASPECTS software, we will perform multivariable ordinal logistic regression using the variables pre-specified in Table 5. The dependent variable will be the absolute difference in ASPECTS between e-ASPECTS and expert human readers (i.e. scalar, 0-10).

For any variables found to be significantly associated with poorer e-ASPECTS results on regression testing (i.e. independently associated with greater difference between e-ASPECTS and expert human reader scores), we will also calculate and compare diagnostic accuracy figures (as above) for each of the subgroup arms (for these analyses only, continuous data will be dichotomised as per Table 5).

Finally, to account for (the as yet unknown) covariates that alter e-ASPECTS diagnostic accuracy figures, we will derive covariate-adjusted ROC curves (AROC)^50^.

**
*2. Identification of CTA obstruction and collateral scoring by e-CTA versus expert human readers.*
** There are two components to the e-CTA output: 1. Where ICA-MCA occlusion is identified, the location is categorised either proximal (ICA/proximal MCA) or distal (distal MCA). Other arteries are not assessed.2. MCA collateral scoring (modified Tan *et. al*. 2009)^51^ is given for all cases on the scale 0 = no collaterals (<10% of affected MCA territory compared to contralateral side), 1 = poor (10–50%), 2 = good (50–90%), 3 = excellent (>90%) collaterals (i.e. includes normal scans).

The expert human rated CTAs available to RITeS include similar scoring methods for comparison with e-CTA outputs, but also additional measures such as degree of arterial patency (i.e. from fully patent through increasingly obstructed to occluded)^22^.

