To limit the possibility of previously calculated results being presented again (rather than freshly derived from the ‘new’ scan), selected scans will have all unique identifiers replaced prior to repeat e-ASPECTS/e-CTA processing. This includes original trial IDs and any other DICOM information that uniquely identifies individual scans (e.g. accession number, series/scan unique identifiers).

We will compare original and repeat results for agreement, as per Table 8. We will use Mann-Whitney U tests to compare scalar and non-parametric continuous group data, and K-alpha to compare paired scan results.

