**Table 3. T3:** Planned assessment of radiological characteristics of the entire RITeS dataset.

Radiological Finding		N (%) or Median (IQR)
Ischaemic brain changes	None	
	Subtle (e.g. loss of grey-white margins)	
	Obvious (e.g. hypoattenuation relative to normal white matter +/- swelling)	
Ischaemic location	MCA territory	
	Other cerebral	
	Brainstem or cerebellum	
	Cortical	
	Subcortical	
Hyperattenuating arteries	List location	
Haemorrhage location	Deep	
	Lobar	
	Intraventricular	
	Extra-axial	
Structural stroke mimic	List type (e.g. tumour, inflammation, collection)	
Pre-stroke brain changes	Atrophy	
	Leukoaraiosis	
	Old Stroke lesions	
CT slice thickness	Thin (≤ 1 mm)	
	Medium (> 1 mm ≤ 5 mm)	
	Thick (> 5 mm)	

**Table 4. T4:** Planned univariable comparison of scans successfully versus unsuccessfully processed by e-ASPECTS.

Variable	Successfully Processed	Not Successfully Processed	Absolute differences, 95% CI and p-value
Patient age (median, IQR)			
Patient sex (n, %)			
Minutes from stroke onset to scan (median, IQR)			
NIHSS (median, IQR)			
Stroke aetiology (n, %): • Ischaemia MCA territory • Ischaemia elsewhere • Haemorrhage • Mimic			
Presence of pre-stroke brain changes (n, %): • Atrophy • Leukoaraiosis • Old stroke lesions			
CT slice thickness (n, %): • ≤ 1 mm • > 1 mm ≤ 5 mm • > 5 mm			
Image quality (n, %): • Good quality • Movement artefacts • Streak artefacts • Patient malposition			

Note: IQR = Inter-quartile range. MCA = middle cerebral artery. NIHSS = National Institutes of Health Stroke Scale.

**Table 5. T5:** Variables for multivariable analysis and subgroups for diagnostic accuracy testing.

Clinical Characteristics		Imaging Findings		Imaging Technique	
Age	≤60 years	ASPECTS	<6	CT slice thickness	≤1 mm
	>60 years		≥6		> 1 mm
NIHSS	0–6	Infarct Location	MCA territory	Poor patient positioning	Yes No
	7–12		Elsewhere		
	>12	Atrophy, Leukoaraiosis, Old stroke lesion	Yes No		
Time from stroke onset to scan	<3 hours				
	3+ hours			Imaging artefact (movement or streak)	
Knowledge of affected side	Yes No				

**Table 6. T6:** Comparison of ICA-MCA axis occlusion identified by e-CTA and expert-human groups.

Human Readers e-CTA	Proximal Occlusion	Distal Occlusion	TOTAL
Proximal Occlusion			
Distal Occlusion			

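### Knowledge of the affected side is tested only as a regression covariate, although with-side and without-side results should exist for the same scans

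*SAP article*

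**What the plan says.** The Image processing section describes a first stage in which "all scans meeting these criteria will be processed agnostic of patient or imaging characteristics". Item 6 of the same list adds: "Affected side information will not be included at this processing stage but will be entered separately later for a proportion of cases".

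The general analysis principles then make a promise: "We will separately test whether knowledge of affected side impacts the accuracy of e-ASPECTS results, see secondary outcomes below".

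Under the first secondary outcome, the analysis of accuracy is a single model: "we will perform multivariable ordinal logistic regression using the variables pre-specified in Table 5". Its dependent variable is the absolute software-expert difference in ASPECTS (0-10), and it uses the entire RITeS sample. In Table 5, "Knowledge of affected side" is a Yes/No row among the clinical characteristics, beside age, NIHSS and time from onset. Variables significantly associated with poorer results then lead to accuracy figures by subgroup arm.

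In the repeatability section, unique identifiers are replaced before scans are processed again. The reason given is "To limit the possibility of previously calculated results being presented again". No similar step is stated for the later entry of side.

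**The concern.** Whether the software was told the affected side is a condition of the run, not a trait of the patient. Age or NIHSS can only be compared between patients. Side knowledge can be compared within a scan, and the order of processing steps implies that both results should exist for each scan given a side. The plan nevertheless handles it like the patient traits and names no within-scan analysis.

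At stake is the answer to a question the plan explicitly undertakes to test separately. A between-scan term can reflect which cases were given a side rather than what the side information did. Because significance in this model decides which variables receive subgroup accuracy figures, a distorted side coefficient could also produce, or suppress, a side-known versus side-unknown accuracy comparison made on different patients.

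**Working it through.** **Plan figures.** The plan gives no sample size, effect or power for this test, so there is no figure to reproduce. The share of scans given a side, the within-scan correlation and the selection mechanism used below are all assumptions.

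**What the stated model can do with the data.** The plan does not say whether a scan with two results contributes one row or two.

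- *One row per scan.* The Yes and No groups are different patients. The coefficient is free of confounding only if side entry is unrelated to case difficulty after adjustment for the other Table 5 variables.
- *Two rows for side-entered scans, no scan term.* The Yes rows are compared with all No rows, including those of scans never given a side. Between-scan differences still enter, and the pairing is not used.

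**Precision when side entry is random.** Let N be all scans, q the share given a side, n₁ = qN, and ρ the within-scan correlation of absolute error. For a simple difference in means, in units of the outcome SD:

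- between-scan SE = √(1/n₁ + 1/(N − n₁)) = √(1/[n₁(1 − q)])
- paired SE = √(2(1 − ρ)/n₁)
- ratio = 1/√(2(1 − ρ)(1 − q)), which does not depend on N

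| Share q | ρ = 0.5 | ρ = 0.8 | ρ = 0.9 |
|---|---|---|---|
| 10% | 1.05 | 1.67 | 2.36 |
| 30% | 1.20 | 1.89 | 2.67 |
| 50% | 1.41 | 2.24 | 3.16 |

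At q = 30% and ρ = 0.8 the ratio is 1/√(2 × 0.2 × 0.7) = 1.89. Squared, that is a 3.6-fold difference in effective sample size. Pairing is not always more precise: the two are equal when 2(1 − ρ)(1 − q) = 1, which at q = 10% is ρ = 1 − 1/1.8 = 0.44. These formulas ignore covariate adjustment, so they are a guide to the ordinal model and not a calculation for it.

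**Bias when side entry is not random.** An illustrative ordinal-logit simulation used 2000 scans, about 30% given a side, 60 replicates and no other covariates. Side was entered either at random or more often for scans with greater unmeasured difficulty. A positive value means larger error with side known. The first two estimates are log-odds coefficients; the paired estimate is in category points.

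| True shift | Side entry | One row | Two rows, no scan term | Paired mean difference |
|---|---|---|---|---|
| 0 | random | −0.02 (rejects 2%) | −0.02 (0%) | −0.01 (3%) |
| 0 | by difficulty | +1.01 (100%) | +0.66 (100%) | 0.00 (3%) |
| −0.3 | random | −0.25 (80%) | −0.25 (82%) | −0.17 (98%) |
| −0.3 | by difficulty | +0.76 (100%) | +0.42 (100%) | −0.20 (100%) |

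Under the assumed selection, both unpaired layouts reject a true null in every replicate and reverse the sign of a real benefit. The paired estimate does neither.

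**Stored results.** If half of the later runs returned the earlier result, then with random entry and a true shift of −0.3 the one-row coefficient would fall from −0.25 to −0.13, and the paired difference from −0.17 to −0.08. Pairing does not cure this.

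**The case against.** Several points on the other side are fair.

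- *The reruns are inferred.* The text says that side is entered later; it does not say that scans are uploaded again. This stands as a caution. Even so, all eligible scans go through the side-free stage first, so a side-free attempt should exist for each scan given a side.
- *The model is multivariable.* Table 5 also contains age, NIHSS, time from onset, ASPECTS, infarct location, pre-stroke changes, slice thickness, positioning and artefact. Adjustment removes part of any case-mix difference. The large simulated biases come from assumed selection on unmeasured difficulty, so they show what is possible and do not predict what will happen.
- *An article condenses.* How many scans receive a side and how they are drawn may be set out in a fuller document, so their absence here is not itself the point. The analysis, however, is stated, and it does not match the data structure.
- *Stored results are speculative.* The repeatability guard concerns an unchanged scan presented again. Entering a side changes the input, so the same reasoning does not carry over automatically. Nothing in the document shows that the platform would ignore a newly entered side.

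A reader might also infer that two rows per scan would produce false positives through duplicated data. Under random entry the simulation shows the reverse: with no true effect, the model SE was about 0.084 against an empirical 0.060, so the test was conservative.

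Finally, a reader might put the paired variance at 50%, 30% or 10% of the unpaired variance for correlations of 0.5, 0.7 and 0.9. That assumes equal groups. The plan uses the entire sample, and at a 10% share the figures are 2(1 − ρ) × 0.9, or 90%, 54% and 18%.

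**Conclusion.** The point holds in limited form. The specified covariate analysis does not ensure that the effect of side knowledge is isolated, although a paired analysis should be available from results the study already plans to hold.

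A reader might conclude that the effect cannot be isolated at all. The document does not support that. If side entry is random and results are fresh, the covariate estimates the effect, with the loss of precision tabulated above. The side-free results are also produced in any case, so pairing remains possible. Nor does the document say that side-known cases are restricted to patients with a lateralised deficit or lesion, so the direction and size of any confounding cannot be derived from it.

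The change should be made, but the reach is narrow. It concerns one question within one secondary outcome; the primary outcome analyses make no use of the later side entry.

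**What to change.** 1. Remove the side term from the Table 5 model and fit that model on side-unknown results only.
2. Test side knowledge separately, as promised, by comparing the with-side and without-side absolute error against the expert score on the same scans. A Wilcoxon signed-rank test on the paired absolute differences would do, or an ordinal mixed model with a scan random effect.
3. Draw the scans for side entry at random from cases with a recorded affected side, and state the number.
4. If side entry involves uploading the scan again, apply the identifier replacement already described for repeatability. This is a precaution against a risk the plan raises elsewhere, not one shown to occur here.

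The cost is a few sentences in the SAP and slight extra file handling if scans are re-uploaded. No new imaging or expert reading is needed.
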